## Abstract

**Background:**

Older people are frequent emergency department (ED) users who present with complex issues that are linked to poorer health outcomes following the index visit, often have increased ED length of stay, and tend to have raised healthcare costs. Encouraging evidence suggests that ED teams involving health and social care professionals (HSCPs) can contribute to enhanced patient flow and an improved patient experience by improving care decision-making and thus promoting timely and effective care. However, the evidence supporting the impact of HSCP teams assessing and intervening with older adults in the ED is limited and identifies important methodological limitations, highlighting the need for more robust and comprehensive investigations of this model of care. This study aims to evaluate the impact of a dedicated ED-based HSCP team on the quality, safety, and clinical- and cost-effectiveness of care of older adults when compared with usual care.

**Methods:**

The study is a single-site randomised controlled trial whereby patients aged ≥65 years who present to the ED of a large Irish hospital will be randomised to the experimental group (ED-based HSCP assessment and intervention) or the control group (usual ED care). The recruitment target is 320 participants. The HSCP team will provide a comprehensive functional assessment as well as interventions to promote a safe discharge for the patient. The primary outcome is ED length of stay (from arrival to discharge). Secondary outcomes include: rates of hospital admissions from the ED, ED re-visits, unplanned hospital admissions and healthcare utilisation at 30 days, and 4 and 6 months of follow-up; patient functional status and quality of life (at baseline and follow-up); patient satisfaction; cost-effectiveness in terms of costs associated with ED-based HSCP compared with usual care; and perceptions on implementation by ED staff members.

**Discussion:**

This is the first randomised controlled trial testing the impact of HSCPs working in teams in the ED on the quality, safety, and clinical- and cost-effectiveness of care for older patients. The findings of this study will provide important information on the effectiveness of this model of care for future implementation.

**Trial registration:**

ClinicalTrials.gov, NCT03739515. Registered on 12 November 2018.

## Background

Internationally, emergency departments (EDs) face significant challenges in delivering high-quality and timely patient care set against a background of increasing patient numbers and limited hospital resources [1, 2]. An increasing ageing population and a higher number of individuals with multimorbidities are among the main demographic drivers of incremental ED attendances [3, 4], which in turn lead to ED crowding. Research has demonstrated that ED crowding contributes to a reduction in the quality of patient care, delays in commencement of treatment, increased length of the hospital admission, poorer adherence to recognised clinical guidelines, and increased overall costs [4, 5].

Evidence from international studies demonstrates that health and social care professionals (HSCPs) such as physiotherapists, occupational therapists and medical social workers can play a role in the ED in reducing length of patient stay, avoiding unnecessary hospital admissions and improving the patient experience [6–9]. Furthermore, promoting interdisciplinary care in the ED has been shown to enhance decision-making and contribute to timely and safe patient care, particularly for older adults [10–12]. A recent systematic review [6] demonstrated that care coordination teams comprising of HSCPs (including physiotherapists, occupational therapists and medical social workers) that provide early assessment and intervention to older adults in the ED can contribute to safer discharges and increased patient and staff satisfaction; however, the quality of the evidence is mixed, primarily due to inherent weaknesses in study designs and heterogeneity of patient groups and outcomes of interest.

The overall aim of this study is to examine the impact of a dedicated team of HSCPs in the ED on the quality, safety, and clinical- and cost-effectiveness of care of older adults in the ED.

The objectives of the study are as follows: 1) to implement an HSCP team including a whole time equivalent senior physiotherapist, senior occupational therapist and senior medical social worker in the ED at the University Hospital Limerick (UHL; Ireland) for a period of 6 months; 2) to examine if early assessment and intervention by the HSCP team improves the quality, safety, and clinical- and cost-effectiveness of care among older adults who present to the ED compared with usual care; and 3) to conduct a process evaluation for the HSCP intervention through focus group interviews with the HSCP team and representation from the wider ED staff regarding the implementation, delivery and acceptability of the intervention.

## Methods and design

### Design

The study represents a single-centre parallel group randomised controlled trial which will compare assessment and/or interventions carried by an HSCP team, comprised of a senior physiotherapist, a senior occupational therapist and a senior medical social worker, in the ED with usual ED care. The Consolidated Standards of Reporting Trials (CONSORT) guidelines will be followed to ensure the standardised conduct and reporting of the research. This protocol has been registered on ClinicalTrials.gov (NCT03739515) and prepared in accordance with the Standard Protocol Items: Recommendations for Interventional Trials (SPIRIT) guidelines (see Fig. 1). The checklist is presented in Additional file 1.

**Fig. 1 Fig1:**
[figure not shown]
Study schedule. ED emergency department, HSCP health and social care professional

### Setting

The study will take place in the ED of the UHL, a regional hospital with a large catchment area in the western region of the Republic of Ireland. Follow-up assessment will take place via telephone interviews.

### Participants

All adults aged ≥65 years who present to the ED at the UHL between December 2018 and May 2019 (inclusive) are considered eligible for inclusion to the study provided that they meet the following inclusion criteria: 1) the capacity (Mini-Mental State Examination ≥17) and willingness to provide informed consent; 2) baseline mobility and functional status; and 3) are medically stable (where relevant, see Table 1) and presenting with any of the complaints presented in Table 1 as per the Manchester Triage System 2–5 [13].

**Table 1 Tab1:** Presenting complaint as per Manchester Triage System [13]

Before medical work-up*	After medical work-up**
Limb problems	Chest pain
Falls	Shortness of breath
Unwell adult	Abdominal pain
Back pain	Headache
Urinary problems	
Ear and facial problems	

*The health and social care professional (HSCP) team will proactively treat these individuals without prior assessment by a physician

**The HSCP team will await medical clearance prior to assessment and intervention

The exclusion criteria are: 1) aged under 65 years; 2) medically unstable; 3) neither the patient nor the carer can communicate in English sufficiently to complete consent or baseline assessment; and 4) presentation and discharge outside of HSCP operational hours (similar to other studies, the HSCP team is operational between the hours of 8 am and 5 pm Monday to Friday and, therefore, individuals who present to the ED and are discharged outside of these hours will not be included in the study).

This study is pragmatic in nature and, to reflect the realities of clinical practice in the ED, both the triage nurses and treating physicians will act as gatekeepers at the UHL site and inform eligible participants about the study. This method was chosen as the medical condition of participants will change over the course of the index admission.

### Consent

If participants and carers (where relevant) wish to hear more about the study, the triage nurse/treating physician will inform the dedicated research nurse or a member of the HSCP team who will provide the participant/carer with an information sheet and further discuss the nature of the project with them. Participants will be offered an opportunity to ask questions about participation in the study. Prospective participants will then be asked to sign a consent form. Participants will have the duration of their index admission to consider participation in the study. Consent and mechanisms relating to data control and processing will be compliant with the EU General Data Protection Regulation 2016/679 and also in compliance with the Data Protection Act 2018 (Section 36(2) Health Research Regulations 2018).

### Randomisation

Should participants explicitly consent to participate in the study, they will undergo a baseline assessment of function and quality of life by the research nurse or a member of the HSCP team. To minimise the possibility of selection bias, a researcher independent of the recruitment process (MC) will complete random group allocation. Computer-generated random numbers in blocks of 20 will be created using an internet-based system (https://www.randomizer.org/); the allocation equivalent to each number will be written in a sheet that will be placed in sealed opaque envelopes. These numbers will be stored in the pre-sealed envelopes in a locked drawer in the ED. Allocation will be revealed by the research nurse employed in the trial after recruitment of eligible participants and after conducting the baseline assessment. Allocation will be revealed by accessing and opening the next envelope in the sequence and providing the randomisation information simultaneously to the research team and patient. After allocation is revealed, participants will either receive the HSCP intervention or routine care (the control group).

### Power calculation

We estimated our sample size based on our primary outcome (ED length of stay) using G*Power version 3.1. Using data from the Patient Experience Time (PET) database employed in the ED at UHL, the average ED length of stay for patients aged 65 and older for the period 2016–2017 was 13.95 h (standard deviation 12.49 h) [14]. Estimating a 40% decrease in ED length of stay in the intervention group (mean 8.37 h), and with a 20% attrition rate to follow-up, a sample size of 258 patients (129 in each group) is required to achieve 90% power with two-tailed tests at an alpha level of 0.05.

### Experimental and control interventions

#### Intervention

Participants in the intervention group will be assessed by one or more members of the dedicated HSCP team (physiotherapy, occupational therapy and medical social work). This will include a holistic assessment of mobility, functional, cognitive and psychosocial abilities. Similarly, interventions prescribed by the HSCP team will be based on subjective and objective assessment of patients; individualised discharge care plans will be instituted from the ED to promote safe and supported discharge home. All assessments and interventions will be included in the medical chart of individual participants and communicated back to the ED team. To reduce the risk of contamination in the control group, the HSCP team’s activities will be limited only to the patients allocated to the intervention.

#### Control group

The comparison group will receive routine care for the duration of their stay in the ED. Currently, there is no dedicated team of HSCPs to assess and intervene with older adults who present to the ED at UHL. Ad-hoc services are provided by allied health professionals (i.e. physiotherapists or medical social workers not involved in the HSCP intervention for this study) if they are bleeped from their departments by the ED medical staff. This process will continue for the duration of the trial and will be recorded.

### Outcomes

A range of outcomes will be assessed to identify the potential impact of the intervention on quality, safety, and clinical- and cost-effectiveness of care. The primary outcome of the study is duration of patient ED stay (mean number of hours from time of arrival to discharge or admission). The secondary outcomes include the rates of hospital admissions from the ED (defined as the proportion of patients who are admitted to hospital after their index visits), the duration of hospital admission after the ED index visit, as well as the number of ED re-attendances, nursing home admissions, unplanned hospital visits (and duration of stay) and mortality within 30 days, 4 months and 6 months of the initial index visit. Healthcare utilisation (visits to a general practitioner (GP), public health nurse, home help, private consultation, outpatient department visit, or allied health services) will also be captured at 30 days, 4 months and 6 months after the index visit. Assessment of patient-oriented outcomes include the Barthel Index for Activities of Daily Living [15] as a global measure of function and the EuroQoL’s 5-level of the EQ-5D (EQ-5D-5 L) to measure health-related quality of life [16], which will be conducted at baseline as well as at follow-up (30 days and 6 months, with quality of life also assessed at 4 months).

In addition, patient satisfaction with their index visit will be explored using the 18-item Patient Satisfaction Questionnaire (PSQ-18) [17] at the time of the visit.

An economic analysis will estimate the incremental cost-effectiveness of the HSCP team from the perspective of the Irish public health service, compared with usual care. We will estimate healthcare costs from reference costs from national data sources. Participants’ responses to the EQ-5D-5 L questionnaire will be used to estimate health state utilities using the Irish value set [18], and quality-adjusted life years (QALYs) for each treatment group will be estimated across all time points.

Finally, a process evaluation will be conducted through a mixed quantitative–qualitative design to describe the implementation of the intervention as well as investigate the mechanisms and contextual influences of the implementation as perceived by the HSCP team and representation from the wider ED staff. A detailed study protocol for the process evaluation is available elsewhere [19].

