## Discussion

Based on the results of a systematic review [6], this is the first randomised controlled trial to examine the impact of an HSCP team on the quality, timeliness and cost-effectiveness of care of older adults in the ED when compared with usual care. Previous randomised controlled studies have focused mainly on single HSCPs working as members of ED teams [21, 22], while studies that have described HSCP teams have employed nonrandomised designs [23, 24]. Our study employs a controlled and robust design which is the most appropriate to demonstrate the efficacy of this model of care. The range of outcomes assessed in the study will enable us to provide detailed conclusions on the impact both at the patient and process levels. Furthermore, we will provide information on effectiveness both through a cost analysis and a qualitative investigation of feasibility involving ED staff members. The findings of the study will offer useful recommendations for future implementation.

A potential issue related to the study includes the fact that, due to the nature of the intervention, patients and ED staff members involved in the study cannot be blinded to allocation. While this may increase the risk of performance bias, an open procedure reflects realities of clinical practice in the ED. Another issue is linked to the working hours of HSCPs (8 am to 5 pm Monday to Friday) which may result in missing eligible patients who present out of these hours. However, we will capture crude estimates of these presentations to report the generalisability of the trial. Furthermore, as agreed with the team and the ED medical/nursing staff before the commencement of participant recruitment, the HSCP team’s scope will be limited only to patients involved in the trial; however, a risk of contamination cannot entirely be ruled out as ED medical and nursing staff collaborating with the HSCP team could be influenced in their procedures if taking care of patients in the control group.

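### ED length of stay is counted from arrival but patients are randomised later, so the unadjusted primary test carries avoidable noise: a loss of precision, not bias

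*Protocol article*

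**What the plan says.** **Clock.** Under Outcomes, the primary outcome is duration of ED stay, the "mean number of hours from time of arrival to discharge or admission".

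**Steps before allocation.** Under Participants, "both the triage nurses and treating physicians will act as gatekeepers at the UHL site and inform eligible participants about the study". Under Consent, "Participants will have the duration of their index admission to consider participation in the study". Under Randomisation, "Allocation will be revealed by the research nurse employed in the trial after recruitment of eligible participants and after conducting the baseline assessment", and the intervention starts only after that. For the complaints in the right-hand column of Table 1, "The HSCP team will await medical clearance prior to assessment and intervention".

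**Hours.** The team works 8 am to 5 pm, Monday to Friday. The exclusion states that "individuals who present to the ED and are discharged outside of these hours will not be included in the study". The Discussion adds that these hours "may result in missing eligible patients who present out of these hours".

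**Planned size.** The Power calculation takes a whole-stay mean of 13.95 h (SD 12.49 h) and a 40% reduction to 8.37 h. It asks for 129 per arm, 90% power, two-sided alpha 0.05 and 20% attrition. The abstract gives a recruitment target of 320.

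**Analysis.** Under Data analysis, ED stay is compared by an independent-samples t test or, if normality fails, by a Mann-Whitney test with a bootstrap interval. Neither has a covariate. Function and quality of life, by contrast, are adjusted for baseline values.

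**The concern.** Each patient's outcome is the sum of two parts: time from arrival to randomisation, which is fixed before the arms differ, and time from randomisation to departure, which the team can influence. The first part may vary widely. A patient seen soon after triage may wait little. One who arrives in the evening and is still there at 8 am is not excluded by the wording under Participants, because that wording removes only people who both present and leave out of hours. Such a patient enters with many hours already counted.

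An unadjusted comparison treats all this variation as unexplained, although it could be known for each patient before allocation. At stake is the sensitivity of the primary test. In addition, the 40% reduction is applied to the whole stay, including hours before the team can act.

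**Working it through.** **1. The plan's own figure.** Difference 13.95 − 8.37 = 5.58 h; 5.58/12.49 = 0.447 SD. The exact noncentral-t calculation for 90% power gives 107 per arm; 107 × 1.2 = 128.4, rounded up to 129, or 258 in total. The stated size reproduces. With the full 5.58 h effect, power is 90% at 107 analysed per arm, 94.7% at 129 and 97.9% at 160 (half of 320).

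**2. If the planned saving on the whole stay holds.** The SD of 12.49 h describes the whole stay, so variation in waiting time is already in the sample size. Time before randomisation does not shrink an absolute saving of 5.58 h, and planned power stands. Saving 5.58 h after an average wait of 3 h would need a cut of 5.58/(13.95 − 3) = 51% in the remaining stay.

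**3. If the 40% acts only on hours after randomisation.** The document gives no arrival-to-randomisation time, so its mean P and SD s are assumptions. Take waiting and remaining time as independent, and keep the control mean and SD at 13.95 and 12.49 h (variance 156.0).

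- Effect: 0.4 × (13.95 − P).
- Variance of remaining time, control arm: V = 156.0 − s². A proportional cut makes it 0.36 × V in the intervention arm.
- SE unadjusted: √[(156.0 + s² + 0.36V)/n].
- SE adjusted for waiting time: √[1.36V/n].
- Approximate power: Φ(effect/SE − 1.96).

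Worked case, P = 5, s = 5, n = 129. The effect is 0.4 × 8.95 = 3.58 h and V = 131.0.

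- Unadjusted: SE = √[(156.0 + 25 + 47.2)/129] = 1.330; 3.58/1.330 = 2.69; power about 77%.
- Adjusted: SE = √[178.2/129] = 1.175; 3.58/1.175 = 3.05; power about 86%.

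Simulation with gamma-distributed times and robust standard errors gives similar results:

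| Assumed wait: mean, SD (h) | Effect (h) | 129/arm: unadjusted, adjusted | 160/arm: unadjusted, adjusted |
|---|---|---|---|
| 3, 2 | 4.38 | 94%, 95% | 97%, 98% |
| 5, 5 | 3.58 | 79%, 88% | 87%, 94% |
| 6, 7 | 3.18 | 66%, 88% | 74%, 94% |

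**4. The Mann-Whitney fallback.** An SD close to the mean suggests skew, so the fallback may well be used. At 129 per arm, simulated power for total stay against post-randomisation stay is about 61% and 73% (5 h, SD 5), and about 52% and 71% (6 h, SD 7).

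**The case against.** **It is not an error, and there is no bias.** Arrival to departure is the natural pragmatic measure and matches the hospital data used for the sample size. Waiting time is balanced in expectation by randomisation. Both points stand. A reader might infer a biased primary result; the documents do not support that.

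**The dilution rests on a substituted effect.** The protocol assumes 40% of the whole stay. Moving the 40% to the remaining hours is a different assumption, and the power loss follows from it. This stands. A reader might conclude that the trial is underpowered, and a calculation holding the SD at 12.49 h in both arms seems to show it: 80% power at an assumed 3 h wait and 63% at 5 h, with 129 per arm. That is the pessimistic version, because a proportional cut also narrows the spread in the intervention arm; allowing for this gives 94% and 79%. It also ignores the 320 target. The 20% attrition is described as loss to follow-up, whereas ED stay is complete at the index visit.

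**The two statements on hours do not conflict.** Participants excludes people who both present and leave out of hours; the Discussion says only that some out-of-hours presenters may be missed. A reader might see a contradiction, but the two are compatible. How many patients waited overnight is unknown, and the consent wording sets a maximum time to decide, not a typical one.

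**Such detail belongs in an analysis plan.** Only in part: the protocol itself fixes an unadjusted primary test.

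**The remedy is not free.** The document does not say that allocation or consent time was recorded, and recruitment has closed. A covariate cannot be added to either named test. Waits for medical clearance that follow randomisation would not be captured. All of this stands, but the cost is small.

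**Conclusion.** The point holds as one of precision. The clock starts at arrival, the intervention cannot act until later, and the stated primary test does not use the time already spent. The mean difference in hours remains a valid, unbiased estimate.

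If waits are short and uniform, adjustment gains about one percentage point of power. With longer and more variable waits it gains about 9 to 22 points at 129 per arm (88 − 79; 88 − 66) and 7 to 20 points at 160 per arm (94 − 87; 94 − 74). These figures assume a 40% cut confined to hours after randomisation, independence of waiting and remaining time, and waiting times that the document does not give. If the intervention saves the planned 5.58 h of total stay, planned power is not in doubt.

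**What to change.** Keep arrival to departure as the primary outcome. Before any comparative analysis:

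- Make the primary analysis a linear regression of ED stay on arm and arrival-to-randomisation time, with robust or bootstrap confidence intervals. The arm coefficient is still a difference in mean hours.
- Where envelope opening was not time-stamped, use consent or baseline-assessment time as a proxy. Both precede allocation, so either is a legitimate covariate.
- Report randomisation-to-departure time as a supporting analysis, also by Mann-Whitney test.

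The cost is one timestamp per patient, which must be available in or approximated from trial records, and the replacement of a simple test by a regression. No further recruitment or patient contact is needed.
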